# Effect of intraoperative paravertebral or intravenous lidocaine versus control during lung resection surgery on postoperative complications: A randomized controlled trial

**DOI:** 10.1186/s13063-019-3677-9

**Published:** 2019-11-06

**Keywords:** Lidocaine, Lung resection surgery, Postoperative pulmonary complications, Postoperative complications

## Abstract

**Background:**

Use of minimally invasive surgical techniques for lung resection surgery (LRS), such as video-assisted thoracoscopy (VATS), has increased in recent years. However, there is little information about the best anesthetic technique in this context. This surgical approach is associated with a lower intensity of postoperative pain, and its use has been proposed in programs for enhanced recovery after surgery (ERAS). This study compares the severity of postoperative complications in patients undergoing LRS who have received lidocaine intraoperatively either intravenously or via paravertebral administration versus saline.

**Methods/design:**

We will conduct a single-center randomized controlled trial involving 153 patients undergoing LRS through a thoracoscopic approach. The patients will be randomly assigned to one of the following study groups: intravenous lidocaine with more paravertebral thoracic (PVT) saline, PVT lidocaine with more intravenous saline, or intravenous remifentanil with more PVT saline. The primary outcome will be the comparison of the postoperative course through Clavien-Dindo classification. Furthermore, we will compare the perioperative pulmonary and systemic inflammatory response by monitoring biomarkers in the bronchoalveolar lavage fluid and blood, as well as postoperative analgesic consumption between the three groups of patients. We will use an ANOVA to compare quantitative variables and a chi-squared test to compare qualitative variables.

**Discussion:**

The development of less invasive surgical techniques means that anesthesiologists must adapt their perioperative management protocols and look for anesthetic techniques that provide good analgesic quality and allow rapid rehabilitation of the patient, as proposed in the ERAS protocols. The administration of a continuous infusion of intravenous lidocaine has proven to be useful and safe for the management of other types of surgery, as demonstrated in colorectal cancer. We want to know whether the continuous administration of lidocaine by a paravertebral route can be substituted with the intravenous administration of this local anesthetic in a safe and effective way while avoiding the risks inherent in the use of regional anesthetic techniques. In this way, this technique could be used in a safe and effective way in ERAS programs for pulmonary resection.

**Trial registration:**

EudraCT, 2016–004271-52; ClinicalTrials.gov, NCT03905837. Protocol number IGGFGG-2016 version 4.0, 27th April 2017.

**Electronic supplementary material:**

The online version of this article (10.1186/s13063-019-3677-9) contains supplementary material, which is available to authorized users.

## Background

Surgical stress triggers a local and systemic inflammatory response, with cytokine expression modulating the inflammatory process. An exaggerated perioperative inflammatory response during lung resection surgery (LRS) has been associated with the appearance of postoperative complications [1, 2]. An association has also been demonstrated between inflammation and postoperative kidney damage [3], supraventricular tachyarrhythmias [4], postoperative cognitive dysfunction [5], and the intensity of peri-operative pain [6]. LRS by video-assisted thoracic surgery (VATS) was shown to provide improvements for the patient with regard to both pain management and quality of life compared to thoracotomy [7] and open lung resection. However, there is less information about what the best type of analgesia is when performing pulmonary resection by VATS.

Thoracic paravertebral block (TPVB) is a peripheral nerve block that has similar effectiveness to thoracic epidural anesthesia (TEA) for the management of thoracotomy pain and is also associated with a lower incidence of complications [8]. Its use is widely accepted in open thoracic surgery. However, there is less information about its use in LRS-VATS. A recent meta-analysis showed that TPVB in VATS is associated with better quality of pain management than a control intervention. It also reduces the consumption of postoperative anesthesia for 48 h and the length of hospital stay [9]. This regional technique is associated with an attenuation of the perioperative response to stress according to measurements of inflammatory biomarkers [10, 11] and stress hormones [12].

Lidocaine is the only local anesthetic (LA) that is safe for intravenous (IV) use. We have known for years that IV lidocaine has systemic analgesic effects, and its intravenous administration intraoperatively decreases opioid consumption. Anti-inflammatory effects associated with the use of local anesthetics have also been described [13]. The use of a continuous IV infusion of lidocaine during surgery is associated with a lower systemic inflammatory response according to plasma cytokine levels, as well as less postoperative pain, a shorter duration of postoperative paralytic ileus, and earlier hospital discharge [14–17]. At the experimental level, our group demonstrated that administration of IV lidocaine in pigs subjected to LRS (lobectomy) decreased proinflammatory cytokine expression in the liver and bronchoalveolar lavage (BAL) fluid, and it also decreased pulmonary edema [18, 19]. These effects were observed both intraoperatively and at 24 h postoperatively. We hypothesized that IV or paravertebral (PV) administration of lidocaine would attenuate the systemic and pulmonary inflammatory response that patients usually develop, which would result in a better postoperative course.

## Methods/design

### Methods

#### Study design and setting

This study will be conducted at a single center (an academic hospital) as a randomized, double-blind, controlled, phase IV clinical trial with three parallel groups. It will be performed in accordance with the legislation in Spain, Royal Decree 1090/2015 of December 4 and Law 14/2007 (Biomedical Research Law). The law requires carrying civil liability insurance that covers possible damages that may result for patients included in the study and guaranteeing compliance with data protection laws. The trial was approved by the clinical research ethics committee of Gregorio Marañón University Hospital on April 2018 and is registered with EudraCT (2016–004271-52) and ClinicalTrials.gov (NCT03905837).

#### Patients

The trial will include patients who are over 18 years old and are legally capable. Patients of both sexes who are scheduled to undergo LRS in the thoracic surgery department at Gregorio Marañón Hospital will be included. Participation will be voluntary and signed informed consent forms will be collected. Participants will be required to pass functional respiratory tests with forced expiratory volume at one second > 50% or forced vital capacity > 50% preoperatively, and they will not have received chronic treatment with oral corticosteroids or immunosuppressants 3 months before surgery. Participants must also have no previous history of liver disease. The exclusion criteria are pregnancy or lactation, known hypersensitivity to amide-type local anesthetics, transfusion of blood products in the past 10 days, and an inability to undergo mechanical ventilation for pulmonary protection.

#### Intervention plan

The participant timeline is shown in Fig. 1. All of the patients included in the study will be managed with the same preoperative and postoperative protocols, which include antithrombotic and antibiotic prophylaxis, fasting to clear fluids until 2 h before the surgery, restrictive fluid therapy with crystalloids (less than 1.5 L of positive balance in the first 24 h), postoperative PV analgesia, pulmonary protection ventilation during the one-lung ventilation (OLV) period (tidal volume less than 6 mL/kg ideal weight), and an early mobilization of the patients. The acute pain unit (APU) at our center will manage the postoperative pain. The PV analgesic infusion will be stopped 48 h after the surgery.

**Fig. 1 Fig1:**
[figure not shown]
Consort list

At the preoperative visit, a member of the research team will visit the candidate to explain the study. If a patient agrees to be included in the study, they will be asked to sign an informed consent form and undergo a mini-mental state examination. No anxiolytics will be administered to the patients before the surgery.

### Randomization

Patients will be randomized into the following three groups (1:1:1 ratio): intravenous lidocaine and PV saline (group 1); IV and PV saline solution with lidocaine (group 2); or IV remifentanyl and PV saline solution (group 3). The randomization will be performed using the software EPIDAT 3.1 before the first patient is recruited, and the randomization codes will be kept in a sealed envelope with a number on the outside of the envelope.

A study nurse will be in charge of preparing the medication according to the result obtained in the envelope. The surgical anesthesiologist will receive the assigned and prepared medication for the corresponding group with only the identification of IV perfusion (500 mL) and PV perfusion (100 mL) without knowledge of the group to which the patient belongs. The content of solutions will be indistinguishable to the investigating team because all of the solutions are clear liquids.

For bias control, the physicians involved will be blinded to the techniques used, including the anesthesiologist responsible for the intraoperative management of the patient, the physician responsible for postoperative control in the postoperative care unit, and the guard physician who will perform the cognitive dysfunction test preoperatively and postoperatively, as well as the follow up until the month of surgery. Those responsible for analysis of the biological samples will also be blinded.

### Interventional treatment

Patients will be recruited consecutively and randomized into three groups of intraoperative management, as follows:
Group 1: Experimental arm—intravenous lidocaine and PV saline (SS). During intraoperative anesthetic maintenance, a continuous IV infusion of lidocaine at 1.5 mg/kg/h will be administered until the end of surgery, and perfusion of 0.9% SS will be administered through an intraoperative PV catheter at a rate of 0.1 mL/kg/h.Group 2: Experimental arm—intravenous SS and PV lidocaine. During anesthesia maintenance, a continuous intravenous infusion of 0.9% SS and an infusion of 2% lidocaine will be administered through an intraoperative PV catheter at a rate of 0.1 mL/kg/h.Group 3: Active comparator—intravenous remifentanil and PV SS. A continuous intravenous infusion of remifentanil will be administered at a rate of 0.1 mg/kg/min during anesthesia maintenance until the end of surgery, and an infusion of 0.9% SS will be administered through an intraoperative PV catheter at a rate of 0.1 mL/kg/ h.

The administration of the study drugs will be stopped immediately in cases where the study participant shows relevant deterioration (e.g., severe hypotension refractory to bolus dose vasoconstrictor treatment, or sudden life-threatening arrhythmia).

### Induction and monitoring

Immediately before anesthetic induction, all patients will be monitored using electrocardiograms, pulse oximetry, and capnography. In addition, patients will be monitored using the bispectral index, cerebral oxygen saturation*,* invasive arterial pressure, and peripheral quantitative neuromuscular status. Regardless of the group assigned, all patients will be induced with 2 mg/kg of propofol, 3 μg/kg of fentanyl, and 0.6 mg/kg of rocuronium. Tracheal intubation will be performed with a double-lumen tube. Correct placement will be verified with a fiberoptic bronchoscope.

The patients will then be placed in the lateral decubitus position for the surgery. In this position, a PV catheter will be inserted into the hemithorax (level T5–T6) with a 3-mL initial test dose of 0.25% bupivacaine plus epinephrine (1:200.000), followed by continuous infusion of lidocaine or SS depending on the randomized group assignment. The assigned IV infusion treatment will be started at this time with PV infusion.

The parameters applied during ventilation will be different at three time points: 1) the baseline (BAS) parameters from orotracheal intubation until the initiation of OLV in two-lung ventilation (TLV) will be volume-controlled ventilation, a tidal volume (TV) of 8 mL/kg (ideal weight), positive end expiratory pressure (PEEP) of 5 cmH_2_O, FiO_2_ of 0.4–0.5, and respiratory rate to maintain an end-tidal carbon dioxide at 35 mmHg; 2) the values applied during OLV will be a TV of 6 mL/kg (ideal weight), ideal PEEP calculated as the one that provides the best lung compliance in the recruitment maneuver, permissive hypercapnia, and FiO_2_ of 0.6–1 to maintain SaO_2_ > 90%; and 3) for lung re-insufflation (END), the same ventilation parameters will be applied as in BAS. Recruitment maneuvers will be performed, and continuous positive airway pressure will be used in the nondependent lung when needed to resolve hypoxemia (SpO_2_ < 90%). Restrictive fluid therapy with crystalloids will be administered at 2 mL/kg/h to maintain diuresis > 0.5 mL/kg/h. A fluid bolus of 250 mL of crystalloids will be administered when diuresis is < 0.5 mL/kg/h.

When closure of the thoracic incision begins, all the intervention infusions will be stopped, and a PV bolus of 0.15 mL/kg of 0.2% ropivacaine will be administered. The radial artery will be catheterized in all cases using the Pro AQT sensor to monitor the cardiac index, stroke volume variation, stroke volume index, and invasive arterial pressure. These values will be recorded at baseline during TLV, at 30 min after initiation of OLV, and at the end of OLV. Depending on the data recorded, vasoactive drugs will be administered to ensure optimal hemodynamic parameters for the intrapulmonary shunt. The respiratory parameters recorded during surgery will be as follows: TLV at baseline, 30 min after initiation of OLV, and the end of OLV, FiO_2_, SpO_2_, PaCO_2_, TV, minute volume, respiratory rate, peak pressure, plateau pressure, mean pressure, end expiratory pressure, lung dynamic compliance (Cdyn), and driving pressure.

### Sample and measurement methods

BAL samples will be taken from the dependent lung 5 min before initiating OLV (BAS) and at the end of OLV (END) once TLV is established. Sampling will be performed using a 4.5-mm fiber-optic bronchoscope wedged into the selected segment of the bronchus of the left lower lobe and middle or right lower lobe with 100 mL of 0.9% saline solution in 25-mL aliquots to analyze inflammatory markers (interleukin (IL)-1, IL-2, IL-4, IL-6, IL-7, IL-8, IL-10, IL-12, tumor necrosis factor (TNF)-α, monocyte chemoattractant protein, and vascular endothelial growth factor). Arterial blood will be drawn to measure PaO_2_, SaO_2_, PaCO_2_, and the following inflammatory markers analyzed in BAL at four time points: baseline (before OLV), 30 min after initiation of OLV, the end of OLV, and 24 h after surgery. BAL and blood samples will be centrifuged, and the supernatant will be analyzed at a specialized laboratory. Biomarker concentrations will be analyzed using western blotting. The relationship between pro-inflammatory and anti-inflammatory markers is measured using the ratios of IL-6/IL-10 and TNF-α/IL-10.

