Systemic inflammatory biomarkers (IL-1, IL-2, IL-6, IL-8, IL-10, TNF-α, and monocyte chemoattractant protein) in serum and BAL fluid. Neuroinflammatory markers (S-100 beta protein, neuronal specific enolase, and glial fibrillary acidic protein) measured in serum during the first 24 h postoperativelyThe gas exchange: measured as PaO_2_/FiO_2_ at 24 h after the intervention

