A limitation of the study is the short-term follow-up of the postoperative inflammatory response. At the pulmonary level, only inflammatory biomarkers will be monitored during surgery, and at the systemic level, this monitoring will be extended up to 24 h postoperatively. The expression of inflammatory mediators varies over time and peaks within hours to days depending on the mediator analyzed. In a previous study, however, we observed a relationship between PPCs and inflammation biomarkers in the same period of time [2]. Another potential limitation of the study is related to the PV administration of ropivacaine at the end of surgery. Patients in the two groups who receive PV saline during surgery will have a lower effective concentration of ropivacaine in the PV space by dilution of local anesthetic in PV space. This suggests a bias for the assessment of analgesia in the first measure performed in the PACU, but we do not think that it will affect measurements taken during the rest of the study.

In this study, we intend to elucidate the role of lidocaine when it is administered using IV or PV routes in the potential attenuation of the systemic inflammatory response, postoperative pain, and other postoperative courses. In addition, by monitoring the levels of lidocaine in the blood, we can estimate whether there is a dose-dependent relationship with the biomarkers of inflammation or other prognostic variables Additional file 1.

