PLACE	Ward	OR	PACU	Ward/PACU	Ward/PACU	Ward	Medical consulting
Study procedures							
Informed consent	X						
Medical records	X						
Demographic data	X						
Clinical course		X	X	X	X	X	X
Intervention		X					
tests							
Hemogram	X	X	X		X	X	
Gasometry	X	X	X				
Biochemistry	X		X		X	X	
Lidocain blood		X					
Chest X-ray	X		X			X	
ECG	X		X		X		
Mini-mental test	X				X		
Biomarcadores							
BLA		X					
Blood		X	X				
PO events							
Mortality		X	X	X	X	X	X
PO complications			X	X	X	X	X

*OR* operating room, *PACU* postoperative care unit, *BLA* bronchoalveolar lavage, *PO* postoperative

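### The baseline lavage is, on the stated order, taken after the study infusions start; the baseline blood draw is not tied to them; and the visit schedule has no day-1 draw for the 24-h laboratory values

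*Protocol article*

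**What the plan says.** **Start of treatment (Protocol article, Induction and monitoring).** After intubation and the bronchoscopic tube check, the patient is turned to the lateral position. The paravertebral (PV) catheter is placed with a test dose, "followed by continuous infusion of lidocaine or SS depending on the randomized group assignment". On the intravenous arm of the double dummy: "The assigned IV infusion treatment will be started at this time with PV infusion". The same section defines "the baseline (BAS) parameters from orotracheal intubation until the initiation of OLV in two-lung ventilation (TLV".

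**Baseline samples (Sample and measurement methods).** For lavage: "BAL samples will be taken from the dependent lung 5 min before initiating OLV (BAS". The second and last lavage follows the end of OLV (END). Arterial blood for gases and inflammatory markers is drawn "at four time points: baseline (before OLV), 30 min after initiation of OLV, the end of OLV, and 24 h after surgery".

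**24-h outcomes.** Under Secondary outcomes, gas exchange is PaO2/FiO2 "at 24 h after the intervention". The Discussion confirms that, for blood markers, "at the systemic level, this monitoring will be extended up to 24 h postoperatively".

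**Schedule (Appendix 3, Table 3).** Gasometry is marked at Visits 1, 2 and 3. Under the row heading "Biomarcadores", blood is marked at Visits 2 and 3. Visits 2 and 3 are both headed day 0. Visit 4 is headed day 1.

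**Analysis (Statistical analysis).** Continuous variables are compared between groups by ANOVA or Kruskal–Wallis. Repeated measurements go into a repeated-measures ANOVA.

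**The concern.** A baseline serves as an untreated reference only if it precedes the randomised treatment. Here the sampling clock is set by OLV and the treatment clock by catheter placement, and the text does not connect the two. If lidocaine has already begun to act on a marker when the BAS sample is taken, the arms may differ at BAS. An analysis that measures change from that point then understates the effect.

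This bears on the trial's mechanistic question, which is whether lidocaine attenuates the pulmonary and systemic inflammatory response. It is sharpest for lavage: there are only two samples per patient, so every within-patient lavage contrast rests on BAS.

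The schedule raises a different risk. Staff who work from Table 3 are not prompted to draw blood on the day when one named secondary outcome and the last biomarker time point fall due.

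**Working it through.** The document gives no figure for this point, so the check is of sequence and of table against text.

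**1. Order of events for lavage.** As written:
- induction, double-lumen tube, bronchoscopic check;
- lateral position, PV catheter, test dose, then the PV and IV study infusions together;
- BAS lavage, 5 min before OLV;
- OLV begins and the BAS ventilation phase ends.

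The BAS phase runs from intubation to OLV, so the start of treatment lies inside it. The BAS label therefore does not imply that the patient is untreated. Let t be the minutes from infusion start to OLV, which the document does not give. Drug exposure at the BAS lavage is t − 5 min. The lavage precedes the infusions only if t is under 5.

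**2. Order of events for blood.** The baseline draw has an upper limit (before OLV) and no lower one. A draw s minutes before OLV is pre-infusion if s > t and on treatment if s < t. Both comply with the text, so the timing is not fixed.

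**3. Effect on the analysis.** Let δ be the true difference between two arms in a marker at END, and let a fraction f of it be present at BAS.
- Difference in END levels between arms: δ.
- Difference in change from BAS: δ − fδ = (1 − f)δ.

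With two time points, a group-by-time term in a repeated-measures model is this same change contrast. The direct comparison of END or 24-h levels does not use BAS, and randomisation protects it whatever f is. If f = 0, nothing is lost. The document gives neither f nor t.

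**4. Why no power figure can be attached.** The only sample-size calculation is for the Clavien–Dindo scale: SD 1.5, difference 1, two-sided 5%, power 90%.
- n = 2 × (1.96 + 1.2816)² × 1.5² / 1² = 47.3, so 48 per group.
- 48 / 0.95 = 50.5, so 51 per group, and 3 × 51 = 153.

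This reproduces the stated figures. It does not concern biomarkers, for which no effect, SD or power is given.

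**5. Table 3 against the text.**
- Gasometry: Visit 1 (day −1), Visit 2 (day 0, operating room), Visit 3 (day 0, PACU).
- Blood biomarkers: Visits 2 and 3.
- Lavage: Visit 2.
- Hemogram: Visits 1, 2, 3, 5 and 6. Biochemistry: Visits 1, 3, 5 and 6.
- Visit 4 (day 1, ward or PACU): clinical course, mortality and complications only.

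Three of the four blood times are intraoperative and fit Visit 2. The fourth, 24 h after an operation that ends on day 0, falls on day 1. The day-1 column has no laboratory mark.

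**The case against.** **Blood.** A reader might infer that the baseline blood sample is also on treatment. The text does not support that. Invasive arterial pressure appears in the monitoring listed ahead of the induction drugs, so a pre-infusion arterial draw is possible and would comply. This objection stands: for blood, the defect is that the timing is left open.

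**Anchoring to OLV.** Ventilation, haemodynamics and sampling all follow the same phases, and a pre-OLV reference is a reasonable way to study the injury that OLV causes. The infusions are described without a loading dose, so exposure at BAS may be short. This stands as a reason for the design. It does not make BAS an untreated baseline, and the article does not say that it is on treatment.

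**Analysis.** The article names no change score and no adjustment for BAS, and model details may sit in an analysis plan that is not shown. The planned group tests on later levels are sound. This limits the concern to the repeated-measures analysis and to any change from BAS. It does not remove it, because the repeated-measures ANOVA is stated and BAS is its first time point.

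**Schedule.** A reader might infer that the 24-h values will not be collected. That goes too far: the draw is explicit in the text, and patients normally stay in the PACU until the next morning, so the Visit 3 mark may be meant to cover it. But that column is headed day 0, the separate day-1 visit is blank, and 24 h after surgery can fall after PACU discharge. What stands is a conflict between table and text, with a risk of missed draws.

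**Conclusion.** The point holds and should be corrected. It reaches only the secondary laboratory outcomes. The primary outcome, the sample size and between-arm comparisons of END and 24-h levels are untouched.

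The lavage part rests on two assumptions: that the narrative order is the order followed, and that more than 5 min pass between infusion start and OLV. Bias arises only if a marker has begun to respond by then.

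A reader might go on to quote a loss of power by assuming some fraction of the effect at BAS and 90% power to begin with. The document supports neither input: its 90% belongs to the Clavien–Dindo comparison, and the interval to OLV is not given. The direction can be stated, namely that an early effect shrinks the change from BAS. Its size cannot.

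The schedule part needs no assumption: Table 3 and the text disagree about day 1.

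**What to change.** - State that baseline arterial blood is drawn before any study infusion starts.
- Where feasible, take the BAS lavage before the infusions too; a bronchoscope is already in use at the tube check. Otherwise keep the present time and label the sample as pre-OLV, on treatment.
- For BAS samples taken on treatment, including those already collected, compare END and 24-h levels directly between arms and not as change from BAS.
- In Table 3, add gasometry and blood biomarkers to Visit 4.

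Cost: no samples are added beyond those the text already requires. Moving the lavage alters a procedural step, which is why it is optional. The first patient was included in January 2019, so baseline timing will differ between patients enrolled before and after the change, and the date of change should be recorded. The amendment must be notified: the Monitoring section says that important modifications are communicated to the Spanish health authority.
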